#### 4. ABBREVIATIONS

|          |                                                                |
|----------|----------------------------------------------------------------|
| ALP      | Alkaline Phosphatase                                           |
| ALT      | Alanine Transaminase                                           |
| AST      | Aspartate Transaminase                                         |
| AE       | Adverse event                                                  |
| AUDIT-C  | Alcohol Use Disorders Identification Test Consumption          |
| BMI      | Body Mass Index                                                |
| CAP      | Continuous Attenuation Parameter                               |
| CC-NAFLD | Compensated cirrhosis due to non-alcoholic fatty liver disease |
| CI       | Chief Investigator                                             |
| CP       | Child-Pugh score                                               |
| CRF      | Case Report Form                                               |
| cT1      | Iron-corrected T1 relaxation time MRI sequence                 |
| ELF      | Enhanced liver fibrosis test                                   |
| GCP      | Good Clinical Practice                                         |
| GP       | General Practitioner                                           |
| HbA1c    | Glycated haemoglobin                                           |
| ICF      | Informed Consent Form                                          |
| INR      | International normalized ratio                                 |
| LUH      | Liverpool University Hospitals NHS Foundation Trust            |
| MHRA     | Medicines and Healthcare products Regulatory Agency            |
| MR       | Magnetic Resonance                                             |
| MRE      | Magnetic Resonance Elastography                                |
| MRI      | Magnetic Resonance Imaging                                     |
| NAFLD    | Non-alcoholic Fatty Liver Disease                              |
| NASH     | Non-alcoholic Steatohepatitis                                  |
| NHS      | National Health Service                                        |
| OUH      | Oxford University Hospitals NHS Foundation Trust               |
| PDFF     | Proton density fat fraction                                    |
| PHU      | Portsmouth Hospitals University NHS Trust                      |
| PI       | Principal Investigator                                         |
| PT       | Prothrombin time                                               |
| R&D      | NHS Trust R&D Department                                       |
| REC      | Research Ethics Committee                                      |
| RCT      | Randomised controlled trial                                    |

|        |                                                                      |
|--------|----------------------------------------------------------------------|
| RGEA   | Research Governance, Ethics & Assurance, University of Oxford        |
| SAP    | Statistical analysis plan                                            |
| SOP    | Standard Operating Procedure                                         |
| TMF    | Trial Master File                                                    |
| TDR    | Low-energy total diet replacement programme with behavioural support |
| TSDMEC | Trial Steering, Data Monitoring, and Ethics Committee                |
| U&E    | Urea, creatinine, and electrolytes                                   |
| UKELD  | UK Model for end-stage liver disease                                 |

## 5. BACKGROUND AND RATIONALE

Compensated cirrhosis due to non-alcoholic fatty liver disease (CC-NAFLD) is a progressive and severe form of NAFLD. It can lead to decompensation and liver cancer requiring liver transplantation. It is estimated to affect 200,000 UK adults. Compared with early-stage NAFLD and no fibrosis (stage 0), patients with compensated cirrhosis (i.e. fibrosis stage 4) due to NAFLD have lower quality of life and increased risk of liver-related and all-cause mortality by 42 and 6 times, respectively. This costs the UK £363 million/year. About 90% of patients have obesity. Obesity and weight gain are independently linked with disease progression.

UK CC-NAFLD cases are projected to double to 400,000 in 2030. This is estimated to increase decompensated cirrhosis and liver cancer by ~150%, increasing the need for liver transplantation.

No pharmacotherapy to treat CC-NAFLD exists. In a James Lind Alliance priority setting partnership, finding effective treatments for NAFLD was the most important research question in the field.

Our systematic reviews and meta-analyses of randomised controlled trials (RCTs) and pre-post trials of weight loss interventions showed that weight loss improves NAFLD and non-alcoholic steatohepatitis (NASH), a moderately severe form of NAFLD. Data on fibrosis changes were limited and no study included patients with compensated cirrhosis. In patients with cirrhosis of any cause and obesity, a pilot weight loss trial with 5kg mean weight loss at 4 months raised no safety concerns and reduced hepatic portal hypertension. In a longitudinal analysis of NASH and fibrosis stage 2-3 (n=215), the probability of histological “fibrosis improvement with no NASH worsening” after 1.5-2 years with 15% weight loss was 43% (95%CI: 26-62%), with no evidence that the association between weight loss and outcome depended upon baseline body mass index or fibrosis. This indicated that moderate to advanced fibrosis, thought to be challenging to change, is modifiable with substantial weight loss.

Substantial weight loss through bariatric surgery, typically 20-35% at 1 year, improves biopsy-proven NASH in most patients and regresses fibrosis stage 2-3 in about half. However, acceptability and access are limited. Less than 1% of all people eligible for bariatric surgery are treated in this way. A higher short-term risk of decompensation and mortality in cirrhosis also exists, likely due to the surgery itself than weight loss.

Reductions in hepatocellular fat, injury, and inflammation (the NASH histological features) are seen as the drivers for fibrosis reduction among patients with NASH and fibrosis stage 2-3. Therefore, substantial weight loss, by reducing these histological features, may delay progression to decompensation or even regress cirrhosis. Dietary approaches leading to substantial weight loss at scale would fill this gap but have not been tested and are not offered routinely.

One such approach is a low-energy total diet replacement programme with behavioural support (TDR). RCTs in routine care show that it leads to mean 15% weight loss (primarily fat mass loss) at 6 months, 10% weight loss at 1 year, 8% at 2 years, and 6% at 3 years. It improves quality of life, and leads to clinically significant reductions in CVD risk and liver fat in early-stage NAFLD, and to type 2 diabetes (T2D) remission. It is cost-effective with no evidence that it increases inequity. NHS England is piloting a TDR programme in 5,000 people for T2D remission. However, active liver disease is excluded from the NHS roll-out. This follows the European Food Safety Authority advice on TDRs, as safety concerns exist regarding liver worsening and frailty.

Rapid weight loss may temporarily increase liver fat and worsen liver disease. A liver that is healthy or with early-stage NAFLD could handle a sharp metabolic change, but this might not be the case in advanced liver disease. Early transient increases in alanine aminotransferase during TDR return to baseline levels by 1 month. Liver biopsy data on TDRs are limited. A 400kcal/day TDR in 41 patients resulted in 34kg median weight loss for 4 months and showed that liver inflammation decreased in some but increased in others and 5 people that lost >1.6kg/week developed new fibrosis. In 7 people with severe obesity on a 500kcal/day TDR for 5 months, liver fat improved, while other biopsy features did not change. After 1.5y, however, they had no evidence of NASH. These data are somewhat reassuring that weight loss ultimately improves NASH but may suggest some early worsening, perhaps related to the rate of weight loss. Modern TDRs are less restrictive (860 kcal/day), which should reduce adverse events (AEs). Our ongoing pilot trial of TDR in patients with moderate fibrosis (but not cirrhosis) indicates improvements in liver fat, inflammation, and fibrosis based on magnetic resonance imaging (MRI) and magnetic resonance elastography (MRE) with no evidence of worsened fibrosis or inflammation assessed biochemically. Three cases with CC-NAFLD followed a 860 kcal/day TDR for 8 weeks in another recent pilot trial with no reported safety concerns.

Weight loss in people with obesity and compensated cirrhosis remains controversial, because sarcopenic obesity is prevalent and weight loss, through muscle loss, may *theoretically* compromise physical function and increase frailty. However, despite the small reductions in muscle mass, substantial weight loss in frail but otherwise healthy older adults with obesity significantly improves physical function and reduces frailty.

These uncertainties of the value of TDR to reduce fibrosis for people with CC-NAFLD require a definitive RCT to be resolved. Before a definitive trial, a small-scale RCT needs to examine whether people with CC-NAFLD can be recruited, stick to the treatment, and present for follow-up, whether the treatment appears to be safe, and to look for early signs of attenuation of the progression of this liver disease.

## 6. OBJECTIVES AND OUTCOME MEASURES

| Objectives                                                                                                                                                                                                                                                                                                                                                                                                                                     | Outcome Measures                                                                                                                                                                                                                                                                                                                                                                                    | Timepoint(s) in weeks of evaluation of this outcome measure (if applicable)                                                                                                                                         |
|------------------------------------------------------------------------------------------------------------------------------------------------------------------------------------------------------------------------------------------------------------------------------------------------------------------------------------------------------------------------------------------------------------------------------------------------|-----------------------------------------------------------------------------------------------------------------------------------------------------------------------------------------------------------------------------------------------------------------------------------------------------------------------------------------------------------------------------------------------------|---------------------------------------------------------------------------------------------------------------------------------------------------------------------------------------------------------------------|
| Co-primary Objectives
i. To assess the safety signals of the intervention

ii. To assess the potential efficacy of the intervention in improving a marker of liver inflammation/fibrosis

iii. To assess the potential efficacy of the intervention in not worsening MRE-estimated liver stiffness, a marker of fibrosis                                                                                                 | i. Criteria of severe changes in biochemistry (ALT, AST, total bilirubin)

ii. Iron-corrected T1 relaxation time (cT1) values by magnetic resonance imaging (MRI)

iii. Liver stiffness by magnetic resonance elastography (MRE)                                                                                                                                                        | 0, 2, 4, 16, & 24

0 & 24

0 & 24                                                                                                                                                                       |
| Secondary Objectives
To examine changes in liver stiffness by transient elastography

To examine changes in liver fat

To examine changes in blood biomarkers

To examine changes in physical performance

To examine adverse events

To examine changes in weight

To examine changes in total fat-free mass

To examine changes in visceral fat

To examine changes in muscle mass | Liver stiffness by transient elastography

i. Proton density fat fraction (PDFF)
ii. Controlled attenuation parameter

i. ELF
ii. UKELD score
iii. CP score

i. Physical performance test
ii. Liver frailty index

Adverse events

Body weight

Total fat-free mass on bioelectrical impedance

Visceral fat on MRI

Muscle mass on MRI | 0, 16, & 24

0 & 24
0, 16, & 24

0 & 24
0, 4, 16, & 24
0, 4, 16, & 24

0 & 24
0 & 24

0, 2, 4, 16, & 24

0, 4, 16, & 24

0, 4, 16, & 24

0 & 24

0 & 24 |
| Exploratory objectives

To examine changes in medication                                                                                                                                                                                                                                                                                                                                                                          | Adjustment in the number and dose of medication                                                                                                                                                                                                                                                                                                                                                     | 0, 4, 16, & 24                                                                                                                                                                                                      |

|                                                |                                                                                                                                        |                                         |
|------------------------------------------------|----------------------------------------------------------------------------------------------------------------------------------------|-----------------------------------------|
| To examine changes in cardiometabolic markers  | i. Blood pressure
ii. HbA1c
iii. Lipid profile                                                                                   | 0, 4, 16, & 24
0, 16, & 24
0 & 24 |
| Process measures                        |                                                                                                                                        |                                         |
| To examine feasibility of recruitment          | i. Number of potentially eligible participants
ii. Proportion of eligible participants randomised
iii. Reasons for non-enrolment | 0
0
0                             |
| To examine intervention engagement             | i. Proportion of sessions attended
ii. Reasons for non-engagement                                                                   | 0, 4, 16, & 24                          |
| To examine retention rate                      | i. Proportion of randomised participants completing a 24-week follow-up visit
ii. Reasons for dropout                               | 2, 4, 16, & 24                          |
| To examine satisfaction with the intervention  | Feedback questionnaire                                                                                                                 | 24                                      |
| To monitor alcohol intake throughout the study | Alcohol intake questions                                                                                                               | 0, 4, 16, & 24                          |

## 7. STUDY DESIGN

This is a prospective randomised controlled trial single-blinded (outcome assessors) to provide indicative evidence of the safety signals and potential efficacy of a weight loss intervention in people with CC-NAFLD. Participants will be recruited from the Oxford University Hospitals NHS Foundation Trust (OUH), Liverpool University Hospitals NHS Foundation Trust (LUH), and Portsmouth Hospitals University NHS Trust (PHU). The intervention will be offered free of charge to participants through two private providers (Nestle Health Science and Oviva). Both providers are currently used within the NHS pilot scheme providing TDR for people with type 2 diabetes. Participants are expected to be involved in the study for approximately 6 months and will be requested to attend a screening visit, a baseline visit, 4 follow-up visits (at 2, 4, 16, and 24 weeks) for an appointment with a study clinician, a blood test, and an imaging scan (if applicable). These visits will take place in the respective local research sites and their collaborating University centres as applicable (e.g., for participants recruited from OUH, visits will be at the John Radcliffe Hospital that includes OUH and the University's Oxford Centre for Magnetic Resonance, and, for participants recruited from LUH, visits will be at LUH and the University of Liverpool). The intervention will be delivered over 24 weeks. Appendix A shows the flow-chart.

In designing this study, we have taken into account the opinions of people with NASH on the frequency of participant visits and the proposed tests. We also spoke to hepatologists around the country about their views on this programme.

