#### **9.5. Blinding and code-breaking**

It is impossible to blind the participants and clinicians to the treatment due to the nature of the intervention. Therefore, procedures for breaking the allocation code are not applicable. The independent assessor of the MRI/MRE scans (for the assessment of the primary outcome) will be blinded to allocation.

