#### **9.6. Description of study intervention, comparator, and study procedures (clinical)**

##### **9.6.1. Description of study intervention**

The intervention is a low-energy total diet replacement programme with behavioural support (TDR) and has three phases.

In phase 1 (sole source TDR, weeks 0-16), participants will consume a nutritionally complete package of 4 formula products per day [soups, shakes, and bars (860 kcal/day)].

In phase 2 (food-re-introduction, weeks 17-22), products will be gradually reduced and replaced with food-based meals. During this phase, participants will consume 3 products per day for weeks 17-18, 2

products per day for weeks 19-20, and 1 product per day for weeks 21-22 together with food-based meals.

In phase 3 (weight maintenance, weeks 23-24), participants will consume food-based meals.

Participants will have contact with the dietitian for around 15 minutes each week (or 30 minutes fortnightly) over the 24 weeks for behavioural support (for details on the structure and content of sessions please see Appendix C). This will be over the phone or the app depending on participant preference.

The intervention including formula products and consultations will be donated by Nestle Health Science and Oviva, respectively (see section 17.1). Participants may choose to receive the formula products during their study assessments, by post, or a combination of both. Management of the stock of products (e.g. delivery, labelling, distribution, storage, and replacements) will follow a study-specific SOP.

Participants in the intervention group will continue to receive care as usual.

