#### Objective physical performance test (20 mins)

Low scores in the modified physical performance test are associated with obesity and the test is responsive to weight loss interventions, with high test-retest reliability. The total score is based on evaluation of nine daily activities. Each activity is scored between 0-4 following protocolised procedures; a total score of 36 indicates the highest performance. The activities are

- i. walking ~15 m
- ii. putting on and removing a coat
- iii. picking up a penny placed 30 cm in front of the participant's dominant foot
- iv. standing up from a ~40cm chair
- v. lifting a ~3 kg book from a table to a shelf ~ 30cm above shoulder height
- vi. climbing one flight of 10 stairs
- vii. performing a progressive Romberg test with feet side-by-side, semi-tandem, and full-tandem for a maximum of 10 seconds.
- viii. climbing up and down four flights of 10 stairs
- ix. performing a 360-degree turn.

Participants will also perform a hand-grip strength test in triplicate. Using their dominant hand, they will be instructed to squeeze with their maximum strength and hold steadily for a few seconds a standard hand-grip dynamometer. The grip strength measurements will be combined with the above chair stands, Romberg test, and sex to calculate the Liver Frailty Index.

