#### Transient elastography (15min)

Transient elastography (Fibroscan®) will be performed by a trained assessor to measure the continuous attenuation parameter (CAP) and liver stiffness. CAP and liver stiffness will provide an indication of liver steatosis and fibrosis, respectively. Participants will be assessed using the appropriate probe.

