### 13.3.2 Trial Steering, Data Monitoring, and Ethics Committee (TSDMEC)

As this is an unblinded trial, the Trial Steering Committee and the Data Monitoring and Ethics Committee will be combined. The TSDMEC of 3 independent members [chair (hepatologist), academic with expertise in clinical trials, clinician] will review and meet online to approve the protocol and meet thereafter every 6 months or following completion of the 4-week follow-up of 8 randomised participants (whichever is earlier) to review data quality and monitor ethics and safety based on unblinded data and advise the TMG. The TSDMEC may meet more frequently and request to review specific analyses (e.g. comparing rates of AEs by trial group or other subgroup) at their discretion and as needed. They will review an extra safety profile report between the scheduled meetings of biochemistry and relevant data of participants discontinuing the intervention or being on enhanced observation. They will review SAEs as they occur. They will formally recommend at the end of each meeting whether the trial should continue with no changes, continue with protocol modifications, or be stopped. Its role, constitution, and composition will follow NIHR guidelines.

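### Section 7 says without limit that outcome assessors are blinded, but section 9.5 blinds only the MRI/MRE assessor; none is specified for elastography, physical performance or frailty, and adverse events are established by unblinded clinicians

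*Protocol*

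**What the plan says.** Section 7 (Study Design) classifies the trial: "This is a prospective randomised controlled trial single-blinded (outcome assessors". No outcome is excepted.

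Section 9.5 (Blinding and code-breaking) is narrower. It first states "It is impossible to blind the participants and clinicians to the treatment due to the nature of the intervention", and then names a single blinded role: "The independent assessor of the MRI/MRE scans (for the assessment of the primary outcome) will be blinded to allocation". Section 12.4 adds a masking device, a second random ID for each scan, and describes it for the MRI data only.

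Section 13.3.2 takes a third position: "As this is an unblinded trial, the Trial Steering Committee and the Data Monitoring and Ethics Committee will be combined".

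On the other outcomes:

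- Section 7 says that participants attend follow-up "for an appointment with a study clinician, a blood test, and an imaging scan (if applicable".
- Section 9.6.3 says "Transient elastography (Fibroscan®) will be performed by a trained assessor to measure the continuous attenuation parameter (CAP) and liver stiffness". Whether that assessor is blinded is not stated.
- For the physical performance test, section 9.6.3 says "Each activity is scored between 0-4 following protocolised procedures". It names no assessor for this test or for the grip measurement that goes into the Liver Frailty Index.
- Section 9.6.1 allows hand-over of products at visits: "Participants may choose to receive the formula products during their study assessments, by post, or a combination of both".

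**The concern.** The three descriptions cannot all stand as written, and the broadest of them sits in the design statement, from which a report would normally take its label. If the trial is reported as assessor-blinded on the strength of section 7, readers will credit several secondary outcomes with a protection that the protocol does not specify.

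These outcomes matter to the trial's own questions. In the objectives and Appendix B, elastography is the only stiffness measure at week 16, and it is the only one at any visit at sites without MRE. The performance test and frailty index address the worry in section 5 that weight loss may cost muscle and function. Adverse events feed the safety progression criterion (11.10) and the stopping rule (11.6). With 16 and 8 participants planned, a few scores influenced by knowledge of the arm could shift an arm summary in either direction.

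**Working it through.** No formula applies. The check compares each outcome with the blinding text and then with the visit and product schedules.

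**Step 1: who assesses what, and is blinding specified?** Visits are those in section 6.

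| Outcome | Assessor in the protocol | Blinding specified? | Weeks |
|---|---|---|---|
| cT1, MRE stiffness (co-primary) | Independent scan assessor | Yes, 9.5 | 0, 24 |
| PDFF, visceral fat, muscle mass | Read from the same MRI | By extension of 9.5 | 0, 24 |
| ALT, AST, bilirubin criteria (co-primary) | NHS laboratory | Not mentioned; little scope for observer influence | 0, 2, 4, 16, 24 |
| Elastography stiffness, CAP | A trained assessor | No | 0, 16, 24 |
| Physical performance test | Not named | No | 0, 24 |
| Liver Frailty Index | Not named | No | 0, 24 |
| Adverse events | Discussion and examination at clinician visits | No; 9.5 rules out blinding clinicians | 0, 2, 4, 16, 24 |

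**Step 2: count.** Section 6 lists thirteen secondary measures: elastography stiffness, PDFF, CAP, ELF, UKELD, Child-Pugh, performance test, frailty index, adverse events, weight, fat-free mass, visceral fat and muscle mass. Three are read from MRI. Five are blood-marker entries or readings from the scale (ELF, UKELD, Child-Pugh, weight, fat-free mass). The remaining 13 − 3 − 5 = 5 depend on an assessor with no blinding specified: elastography stiffness, CAP, performance test, frailty index and adverse events.

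**Step 3: when could product hand-over reveal the arm?** Under 9.6.1, products are the sole diet in weeks 0-16, are reduced over weeks 17-22, and are absent in weeks 23-24. Week-0 tests precede randomisation (9.4).

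- Week 16, window 16 ± 2 = weeks 14 to 18: products are in use throughout, so hand-over can coincide with elastography and CAP.
- Week 24, window 24 ± 3 = weeks 21 to 27: products remain only in weeks 21-22, the early edge. For the performance test and frailty index, whose only post-randomisation visit is week 24, hand-over is a marginal route.
- Adverse events at weeks 2, 4 and 16: hand-over can coincide, but the clinician is already unblinded.

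**Step 4: must the operator know the arm?** Under 9.4 an independent researcher phones the allocation to the chief investigator, who phones the participant. Nothing in that route requires an elastography or performance-test operator to be told.

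One caution on schedules: the visit descriptions in 9.8, read literally, differ from section 6 and Appendix B. The week-16 visit would include MRI/MRE and the performance test. The week-24 visit, defined by reference to the 4-week visit, would omit imaging and elastography. I have followed section 6 and Appendix B, which agree on these tests. The 9.8 text must be reconciled with them.

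**The case against.** The best defence is that 9.5 clarifies section 7: the assessors meant are the scan readers, and 13.3.2 means only that participants and clinicians know the arm. That is a plausible account of the intention. It still leaves section 7 too broad and 13.3.2 in need of qualification.

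A second defence is that little hangs on it. All five measures are secondary, confidence intervals are declared nominal and descriptive (11.7), no progression criterion uses elastography, performance or frailty, and the oversight committee sees unblinded data by design. This stands, and it limits the weight of the point.

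Three stronger readings are tempting, and the document does not support them.

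- A reader might infer that elastography, performance and frailty are measured by staff who know the arm. The protocol is silent on who does these tests and what they know. Only adverse events are open on the text.
- A reader might infer that product hand-over unmasks the whole set of tests. The schedules confine it mainly to elastography at week 16.
- A reader might want to express the bias in points on the 36-point performance scale. The document gives nothing from which to derive such a figure, and the scoring is protocolised.

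**Conclusion.** Section 7 is wrong as written. It claims assessor blinding without limit, while 9.5 provides it for one role and 13.3.2 calls the trial unblinded. The extent is five of thirteen secondary measures: for four the protection is unspecified, and for adverse events it is excluded by the protocol's own account of clinicians. No size of bias can be given. Exposure is likely greatest for the observer-scored performance test and adverse events.

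The co-primary outcomes are not called into question. Two are scan readings covered by 9.5, and the third rests on laboratory values. The point is worth correcting because the stated design property would pass into reports and the correction is cheap. It does not threaten the trial's main comparison. The conclusion assumes that section 6 and Appendix B give the intended schedule and that no other trial document supplies masking for these tests.

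**What to change.** 1. In section 7, describe the trial as *open-label, with only the assessors of the MRI/MRE scans unaware of allocation*, and bring 13.3.2 into line. Report elastography stiffness, CAP, performance test, frailty index and adverse events as open-label unless masking is documented.
2. At each visit, do the assessor-dependent tests scheduled for it (elastography at weeks 16 and 24; performance test and grip at week 24) before any products are handed over and before allocation is discussed. Use an operator who has not been told the allocation where existing staffing allows. The document gives no staffing information, so a dedicated masked operator at all three sites cannot be assumed to be free of cost.
3. Add one CRF field recording whether the operator knew the allocation at the time of testing.

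The cost is a wording change, an order of procedures within existing visits and one data field. Visit scheduling becomes slightly less flexible. Masking may also be imperfect, since section 5 cites mean weight loss of 15% at 6 months with this type of programme, which an operator may notice. The CRF field would show how often masking failed. Adverse events remain open-label, and the remedy there is accurate labelling.
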